### Primary endpoint – DILI strategy study

In the DILI strategy study the primary endpoint is the proportion of time in the 60 days following randomisation during which neither rifampicin nor isoniazid are given (or the subject is dead).

### Secondary endpoints – main trial

The secondary endpoints of the main trial are as follows:

a)Overall survival during a follow-up period of 12 months. Overall survival is defined as the time from randomisation to death, during a follow-up period of 12 months. Survivors known to be alive at 12 months will be censored at that time-point and subjects who withdrew or were lost to follow-up before 12 months will be censored at the date they were last known to be alive.b)Neurological disability at 12 months. Disability will be assessed by the modified Rankin scale (
Table 1) on days 30 and 60 from randomisation, and then monthly until the end of anti-tuberculosis drugs. The main endpoint is the 12-month assessment and subjects who died before 12 months will be treated as having a score of 6 (‘Dead’).c)Severe (grade 3&4) and serious adverse events. Comparison of the frequency of severe and serious adverse events between treatment groups will form an important part of the study analysis.d)Requirement for ‘rescue’ corticosteroids. Neurological complications occurring after the start of anti-tuberculosis chemotherapy for TBM are common. The cause varies, but includes hydrocephalus, infarcts, tuberculoma formation and hyponatraemia. If the symptoms are thought to be caused by tuberculomas, doctors may re-start or increase the dose of corticosteroids. In this trial, any re-start or dose increase of corticosteroids during the 12-month follow-up will be defined as ’rescue’ corticosteroids.

### Secondary endpoints – DILI strategy study

The secondary endpoints of the DILI strategy study are as follows:

a)Development of acute liver failure (defined as new onset coagulopathy (International normalised ratio (INR)>1.5 and hepatic encephalopathy) after randomisation.b)ART interrupted due to drug-related injury (applies to patients enrolled from linked ACT HIV trial).c)Time to new neurological event (defined as a fall in GCS of ≥2 points for ≥48 hours, new focal neurological sign, or new onset of seizures) or death from randomisation until the 12 month follow-up of the main trial.d)Overall survival, i.e. time to death from any cause, until the 12 month follow-up of the main trial.e)Neurological disability at the 12 month follow-up of the main trial.

## Inclusion and exclusion criteria

### Inclusion criteria

Study participants for LAST ACT must be adults (aged 18 years or older), HIV-uninfected, with a clinical diagnosis of TBM (≥5 days of meningitis symptoms, and CSF abnormalities) and anti-tuberculosis chemotherapy either planned or started by the attending physician. Participants will be considered eligible for enrolment in this trial if they fulfil all the inclusion criteria and none of the exclusion criteria. The inclusion and exclusion criteria apply at the point of consent, just before the patient’s blood is sent for LTA4H genotyping. Therefore, it is possible that when the LTA4H genotype result returns and the patient is randomised, the patient will have had >3 days of corticosteroids and/or >6 days of anti-tuberculosis treatment. This is acceptable, although the total duration of corticosteroid and anti-tuberculosis treatment before randomisation must be recorded. The time for an LTA4H result to return is not anticipated to be >3 days (e.g. taken on a Friday afternoon and processed on a Monday morning). As TBM is a serious infection requiring hospitalisation, all eligible participants will be treated in hospital, at least for the initial 3 weeks of their illness.

Study participants for the DILI strategy study must be receiving first-line anti-tuberculosis drugs and fulfil the definition of drug-related liver injury: elevation of blood transaminase concentrations ≥3 times the ULN with symptoms and signs of hepatitis (vomiting, abdominal pain, jaundice), or ≥5 times the ULN or a rise in serum bilirubin >2.0mg/dL (>34 µmol/L) without symptoms
^9^, and less than 90 days of anti-tuberculosis drugs given.

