### Exclusion criteria

Exclusion criteria for the main trial are:

a)An additional brain infection (other than TBM) confirmed or suspected: positive CSF Gram or India Ink stain; positive blood or CSF Cryptococcal antigen test; cerebral toxoplasmosis suspected and attending physician wants to give anti-toxoplasmosis treatment with anti-tuberculosis treatment.b)More than 6 consecutive days of two or more drugs active against
*M. tuberculosis* immediately before screening.c)More than 3 consecutive days of any type of orally or intravenously administered corticosteroid immediately before randomisation.d)Dexamethasone considered mandatory for any reason by the attending physician.e)Dexamethasone considered to be contraindicated for any reason by the attending physician.f)Patient has previously been randomised into the trial for a prior episode of TBM.g)Lack of consent from the participant or family member (if the participant is incapacitated by the disease).

Exclusion criteria for the DILI strategy study are:

a)TBM known to be caused by isoniazid resistant or MDR
*M. tuberculosis* or standard first-line anti-tuberculosis drugs unable to be given for any reason other than DILI.b)Signs of chronic liver disease of any cause (hepatosplenomegaly, prolonged jaundice, caput medusa, spider angiomata, ascites, oedema).c)Lack of consent from the participant or family member (if the participant is incapacitated by the disease).d)Elevation of blood transaminase concentrations ≥3 times the ULN with symptoms and signs of hepatitis (vomiting, abdominal pain, jaundice), or ≥5 times the ULN or a rise in serum bilirubin >2.0mg/dL (>34 µmol/L) without symptoms, at baseline (day 0).

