### Trial management

#### Interventions

All participants will receive the standard of care anti-tuberculosis drugs according to national guidelines. Each participant will be LTA4H genotyped. The enrolment and randomisation of the participant into the trial will be finalised according to genotype. TT-genotype participants will be treated with anti-tuberculosis drugs and open label dexamethasone (
Table 2). LTA4H CC- and CT-genotype participants will be randomised to receive dexamethasone or placebo for 6–8 weeks, in addition to anti-tuberculosis drugs, dependent upon disease severity (
Table 2). Study drug will be dispensed at randomisation from the site pharmacy in intravenous and oral (tablet) formulations. Placebo will be identical in appearance to active drug and dosed and dispensed in the same way.

**Table 2. T2:** Study drug treatment regimen following randomisation.

	MRC Grade I Daily dexamethasone dose/route	MRC Grades II and III Daily dexamethasone dose/route
Week 1	0.3 mg/kg/24 hrs IV	0.4 mg/kg/24 hrs IV
Week 2	0.2 mg/kg/24 hrs IV	0.3 mg/kg/24 hrs IV
Week 3	0.1 mg/kg/24 hrs IV	0.2 mg/kg/24 hrs IV
Week 4	3mg/24 hrs oral	0.1 mg/kg/24 hrs IV
Week 5	2mg/24 hrs oral	4 mg/24 hrs oral
Week 6	1 mg/24 hrs oral	3 mg/24 hrs oral
Week 7	Stop	2 mg/24 hrs oral
Week 8		1 mg/24 hrs oral

Participants for the DILI strategy study will be randomised to one of three strategies (
Figure 2): Strategies are as follows:

1)Observe: measure transaminases, bilirubin, and INR every 3 days; do not change/stop anti-tuberculosis drugs unless transaminases rise to ≥10x normal, or total bilirubin rises >2.5mg/dl (>43 µmol/L), or INR >1.5 or symptoms of hepatitis worsen (nausea, vomiting, abdominal pain), in which case go to Strategy 3.2)Stop pyrazinamide alone. Observe, measuring transaminases, bilirubin, and INR every 3 days. If transaminases do not fall to <5x ULN by day 5, or total bilirubin rises >2.5mg/dl (>43 µmol/L), or INR >1.5 or symptoms of hepatitis worsen at any time (nausea, vomiting, abdominal pain), go to Strategy 3.3)Current standard of care (current US CDC guidelines
^9^,
Supplementary File 2).

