#### Anti-tuberculosis treatment

First line anti-tuberculosis treatment will follow current Vietnamese national guidelines. Rifampicin (10mg/kg/24 hrs; maximum 600mg), isoniazid (5mg/kg/24hrs; maximum 300mg), pyrazinamide (25mg/kg/24hrs; maximum 2g) and ethambutol (20mg/kg/24 hrs; maximum 1.2g) will be given for at least the first 2 months of treatment, provided drug resistance is not suspected or proven. Pyrazinamide will then be stopped and rifampicin, isoniazid and ethambutol (at the same doses) will then be given until at least 12 months anti-tuberculosis treatment in total has been given. The best treatment of TBM caused by isoniazid-resistant tuberculosis is uncertain, and the attending physician should decide which option to take. For participants with MDR tuberculosis, second-line treatment should be given as soon as possible, following national guidelines and local policies.

Participants with abnormal liver function tests (LFTs) at screening are eligible to enter the trial. These patients should be given standard first-line anti-tuberculosis treatment unless blood transaminase concentrations are ≥3 times the ULN with symptoms and signs of hepatitis (vomiting, abdominal pain, jaundice), or ≥5 times the ULN or a rise in serum bilirubin >2.0mg/dL (>34 µmol/L) without symptoms. In these participants, initial anti-tuberculosis treatment should consist of levofloxacin, ethambutol, and an aminoglycoside (either kanamycin, amikacin or streptomycin). LFTs should be monitored every 3 days and rifampicin started as soon as blood transaminases are <5x the ULN and/or the symptoms and signs of hepatitis resolve. Once the participant is tolerating a rifampicin-containing regimen isoniazid can be introduced and, if isoniazid is tolerated, the aminoglycoside can be stopped. If pyrazinamide is not used in treatment, at least 12 months of anti-tuberculosis treatment must be given. Participants with liver dysfunction at the start of treatment that require modified initial anti-tuberculosis treatment regimens are ineligible for the DILI strategy study.

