### Sample size justification – DILI strategy study

A review of 36 subjects who interrupted rifampicin and isoniazid because of clinical hepatitis or jaundice events from our previous trial
^4^ gave the following data: the median (interquartile range (IQR)) onset date of the drug-related liver injury was 50 (15–84) days from initiation of anti-tuberculosis treatment, the median (IQR) duration of the rifampicin and isoniazid interruption was 16 (12–24) days, and 12 subjects subsequently died (8 of them within 60 days). Of note, the duration of the treatment interruption was <t;30 days for 32 (89%) of the 36 subjects and the remaining 4 subjects never re-started rifampicin or isoniazid but continued to receive alternative anti-tuberculosis treatment for >100 days.

We hypothesise that strategies 1 and 2, respectively, will result in a relative reduction in the duration of the treatment interruption of 50% for subjects with interruptions <30 days, but that they do not affect longer interruptions (as the corresponding subject might have permanent intolerance to rifampicin and isoniazid) or mortality. Based on simulations of hypothetical trials using re-sampling from the data described above, the hypothesised treatment effect, and the Wilcoxon rank sum test for analysis, we determined that the power to detect such an effect size with a sample size of at least 50 subjects per arm is >85%. Of note, given this is an ancillary and essentially ‘opportunistic’ study, we have chosen a liberal (i.e. not multiplicity corrected) two-sided significance level of 5% for each of the two primary comparisons of strategies 1 and 2, respectively, versus strategy 3.

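### As written, the liver-injury rule counts bilirubin above 2.0 mg/dL only in patients without symptoms, so a symptomatic patient with transaminases below 3x ULN meets no limb

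*Protocol article*

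**What the plan says.** The same three-limb rule appears in three places in the protocol article.

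- **Inclusion criteria (DILI strategy study).** The first limb sets transaminases at 3x ULN or more, and the text goes on "with symptoms and signs of hepatitis (vomiting, abdominal pain, jaundice), or ≥5 times the ULN or a rise in serum bilirubin >2.0mg/dL". The other two limbs, with their closing qualifier, read in full: "or ≥5 times the ULN or a rise in serum bilirubin >2.0mg/dL (>34 µmol/L) without symptoms".
- **Exclusion criteria (DILI strategy study), item d.** The same limbs exclude a patient who already meets them at the start; the clause ends "without symptoms, at baseline (day 0").
- **Anti-tuberculosis treatment.** The rule decides the first regimen of participants with abnormal liver function tests at screening: "These patients should be given standard first-line anti-tuberculosis treatment unless blood transaminase concentrations are ≥3 times the ULN with symptoms and signs of hepatitis", with the other two limbs following. The clause ends "without symptoms. In these participants, initial anti-tuberculosis treatment should consist of levofloxacin, ethambutol, and an aminoglycoside".

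None of the three says that a bilirubin above 2.0 mg/dL also counts when symptoms are present.

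A related rule stands under Interventions. A patient already in strategy 1 moves to strategy 3 on transaminases of at least 10x normal, "or total bilirubin rises >2.5mg/dl (>43 µmol/L), or INR >1.5 or symptoms of hepatitis worsen (nausea, vomiting, abdominal pain), in which case" the switch is made. Strategy 2 uses the same bilirubin, INR and symptom triggers. There the bilirubin trigger carries no symptom condition.

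**The concern.** In the transaminase limbs, symptoms make the rule easier to meet: the threshold falls from 5x to 3x ULN. In the bilirubin limb, read literally, they do the opposite. A patient with bilirubin above 2.0 mg/dL and transaminases below 3x ULN satisfies the rule while well and stops satisfying it on starting to vomit.

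Applied word for word, this has three effects on that symptomatic patient:

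1. The patient cannot enter the DILI strategy study.
2. If the picture is present at day 0, exclusion criterion d does not exclude the patient.
3. If it is present at screening, the patient stays on standard first-line drugs, whereas the symptom-free patient with identical laboratory values receives levofloxacin, ethambutol and an aminoglycoside. The article's section on complications of TBM attributes hepatitis on treatment to rifampicin, isoniazid or pyrazinamide, so this is a patient-care instruction as well as an eligibility detail.

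**Working it through.** The point concerns the logic of a definition, and the plan states no figure to reproduce. The check is to list every combination and apply the rule.

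**Inputs**, all from the DILI inclusion criteria: transaminases in three bands (below 3x, 3x to below 5x, at least 5x ULN), bilirubin in two (up to 2.0, above 2.0 mg/dL), symptoms no or yes. That gives 3 × 2 × 2 = 12 combinations.

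**Three readings**

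- A: *without symptoms* qualifies the bilirubin limb only. Met if (≥3x and symptoms) or (≥5x) or (bilirubin >2.0 and no symptoms).
- B: it qualifies the ≥5x limb as well. Met if (≥3x and symptoms) or ((≥5x or bilirubin >2.0) and no symptoms).
- C: it means *even without symptoms*. Met if (≥3x and symptoms) or (≥5x) or (bilirubin >2.0).

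| Transaminases (x ULN) | Bilirubin (mg/dL) | Symptoms | A | B | C |
|---|---|---|---|---|---|
| <3 | ≤2.0 | no | – | – | – |
| <3 | ≤2.0 | yes | – | – | – |
| <3 | >2.0 | no | met | met | met |
| **<3** | **>2.0** | **yes** | **–** | **–** | **met** |
| 3 to <5 | ≤2.0 | no | – | – | – |
| 3 to <5 | ≤2.0 | yes | met | met | met |
| 3 to <5 | >2.0 | no | met | met | met |
| 3 to <5 | >2.0 | yes | met | met | met |
| ≥5 | ≤2.0 | no | met | met | met |
| ≥5 | ≤2.0 | yes | met | met | met |
| ≥5 | >2.0 | no | met | met | met |
| ≥5 | >2.0 | yes | met | met | met |

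**Counts.** A: 1 + 3 + 4 = 8. B: 1 + 3 + 4 = 8. C: 2 + 3 + 4 = 9. The difference is the single row in bold.

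**What follows**

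- The gap does not depend on how far the qualifier reaches, since A and B agree in every row.
- The ≥5x limb has no gap. Even under B, a symptomatic patient at ≥5x ULN is caught by the first limb.
- These are counts of combinations, not patient frequencies. The documents give no joint distribution of transaminases, bilirubin and symptoms, so the share of patients in the bold row cannot be estimated.

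**The case against.** **The intended reading is the natural one.** The sentence contrasts a lower threshold for patients with symptoms against thresholds that suffice without them, so the closing phrase most likely means *even without symptoms*. This stands, and it limits the practical effect. It does not remove the fault: the wording is used three times to decide eligibility or treatment, and two hospitals, together with the identical ancillary study in the linked ACT HIV trial, should not have to infer it.

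**The article is condensed, and the cited guideline and Supplementary File 2 are not shown.** The full protocol may lay the rule out differently. That is possible, but the point is about wording the article states, not about something it omits.

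**Stronger readings that the documents do not support**

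- *The entry rule contradicts the escalation rule under Interventions.* A reader might infer this because bilirubin above 2.5 mg/dL moves a patient to strategy 3 whatever the symptoms. But escalation triggers apply after randomisation and differ from entry criteria by design: 10x rather than 3x or 5x, 2.5 rather than 2.0 mg/dL, and INR above 1.5 alone escalates although INR plays no part in entry. The escalation rule supports the inclusive intent and no more.
- *The gap is larger than one combination.* Splitting bilirubin again at 2.5 mg/dL gives 18 combinations, with 13 met as written and 15 as intended. That cut is not in the entry rule; it only divides the same gap in two.
- *The sub-study's own source patients would be shut out.* The sample size rests on "36 subjects who interrupted rifampicin and isoniazid because of clinical hepatitis or jaundice events", but no transaminase or bilirubin values are given for them, so nothing shows that any fell in the gap.
- *Patients whose only feature is jaundice are excluded.* The first limb lists jaundice under symptoms and signs together, while the qualifier mentions symptoms alone. The text does not settle how such a patient is classed, and no claim is made here.
- *The results would be biased.* DILI entry is decided before the DILI randomisation, so a literal reading affects all three strategies alike.

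**Conclusion.** The concern holds as a minor wording error. Read literally, a patient with bilirubin above 2.0 mg/dL, transaminases below 3x ULN and hepatitis symptoms such as vomiting or abdominal pain meets no limb of the rule, although the same patient without symptoms does: one wrong combination of 12, under either scope of the qualifier.

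The consequence arises only where the clause is applied word for word, and is confined to DILI study entry, its day-0 exclusion and the initial regimen. The number of patients is unknown and probably small. The main trial's primary analysis and the validity of the randomised DILI comparison are untouched. The conclusion that this is an error and not a choice rests on one inference: that hepatitis symptoms were not meant to cancel a raised bilirubin. The direction of the transaminase limbs and the unconditional bilirubin trigger under Interventions both support it.

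**What to change.** In the DILI inclusion criteria, DILI exclusion criterion d and the Anti-tuberculosis treatment section, end the bilirubin limb (above 2.0 mg/dL, i.e. above 34 µmol/L) with *with or without symptoms* in place of the present qualifier. In criterion d, keep the day-0 condition after it.

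The ≥5x ULN limb needs no substantive change. If the new phrase is read as covering that limb too, nothing alters, because symptomatic patients at that level already qualify through the first limb. The escalation triggers under Interventions can stay as they are.

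The cost is one clause in three places, with no extra visits, tests or patients. The identical ancillary study in ACT HIV should be checked for the same wording.

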### Exclusion criteria

Exclusion criteria for the main trial are:

a)An additional brain infection (other than TBM) confirmed or suspected: positive CSF Gram or India Ink stain; positive blood or CSF Cryptococcal antigen test; cerebral toxoplasmosis suspected and attending physician wants to give anti-toxoplasmosis treatment with anti-tuberculosis treatment.b)More than 6 consecutive days of two or more drugs active against
*M. tuberculosis* immediately before screening.c)More than 3 consecutive days of any type of orally or intravenously administered corticosteroid immediately before randomisation.d)Dexamethasone considered mandatory for any reason by the attending physician.e)Dexamethasone considered to be contraindicated for any reason by the attending physician.f)Patient has previously been randomised into the trial for a prior episode of TBM.g)Lack of consent from the participant or family member (if the participant is incapacitated by the disease).

Exclusion criteria for the DILI strategy study are:

a)TBM known to be caused by isoniazid resistant or MDR
*M. tuberculosis* or standard first-line anti-tuberculosis drugs unable to be given for any reason other than DILI.b)Signs of chronic liver disease of any cause (hepatosplenomegaly, prolonged jaundice, caput medusa, spider angiomata, ascites, oedema).c)Lack of consent from the participant or family member (if the participant is incapacitated by the disease).d)Elevation of blood transaminase concentrations ≥3 times the ULN with symptoms and signs of hepatitis (vomiting, abdominal pain, jaundice), or ≥5 times the ULN or a rise in serum bilirubin >2.0mg/dL (>34 µmol/L) without symptoms, at baseline (day 0).

### Recruitment, retention and randomisation

#### Recruitment and retention

Recruitment activities will only occur in an inpatient hospital setting (Hospital for Tropical Diseases and Pham Ngoc Thach Hospital, Ho Chi Minh City, Vietnam). The target sample size of around 720 participants will be enrolled within an anticipated accrual rate of 4 years. Once discharged from hospital the participants will be contacted by phone to remind them of their next visit. Patients who miss a visit will be contacted by phone for a maximum of three times after which a maximum of three home visits will be conducted. As part of routine clinical care participants with suspected TBM will have an HIV test, a lumbar puncture, and a GeneXpert MTB/RIF test on CSF. When possible, participants will be screened for eligibility on the day their CSF results return and at the time the decision is made to start anti-tuberculosis chemotherapy for suspected/confirmed TBM. For the DILI strategy study, based on enrolment of all consenting and eligible patients, we anticipate a total sample size of 170 participants (around 70 HIV-uninfected participants from the LAST ACT trial and a further 100 patients from the linked ACT HIV trial
^8^.).

#### Randomisation

Once a participant or their relative has provided written informed consent to enter the study, 5mls of blood will be taken for rapid LTA4H genotyping. The blood will be transported immediately to the OUCRU laboratory within HTD where daily LTA4H genotyping (except at weekends) will be performed. Randomisation will occur once the result of the LTA4H genotyping is available. LTA4H CC- and CT-genotype participants will be randomised to two parallel groups in a 1:1 ratio, receiving either dexamethasone or placebo for 6–8 weeks (according to disease severity). TT-genotype participants will be treated with open-label dexamethasone for 6-8 weeks (according to disease severity). All patients will receive standard anti-tuberculosis chemotherapy. Randomisation will be stratified by participating hospital/site, LTA4H genotype (CC or CT), and modified MRC disease severity grade (
Supplementary File 1) assessed on day 0 when consent is given.

The randomisation list will be computer-generated based on random permuted blocks with variable block size following Oxford University Clinical Research Unit (OUCRU) standard operating procedures. The OUCRU biostatistician in charge of randomisation list preparation will set up statistical code to generate the randomisation list and transfer it to the Study Pharmacist. The Study Pharmacist will then change the random seed, i.e. the initialisation of the random numbers generator, in the statistical code in order to blind the biostatistician and then run the code to prepare the final randomisation list. The generated randomisation lists will be securely incorporated within the trial database. A reliable manual back-up system will also be available. Randomisation to the three strategies for DILI will be 1:1:1 with stratification by initial randomisation (dexamethasone or placebo).

